## Abstract

**Background:**

Cohort studies have public health importance as they effectively provide evidence on determinants of health from a life course perspective. Researchers often confront the poor follow-up rates as a major challenge in the successful conduct of cohort studies. We are currently recruiting in a birth cohort study, titled as “Maternal Antecedents of Adiposity and Studying the Transgenerational role of Hyperglycemia and Insulin” (MAASTHI) in a public hospital; with the aim of assessing maternal glycemic levels on the risk of adverse fetal outcomes. Nested within the ongoing cohort, the proposed trial aims to evaluate the effectiveness of two interventions in improving the follow-up in the cohort study in a public hospital.

**Methods:**

A randomized trial of 795 pregnant women, with 265 women each in three arms observed through pregnancy, until their baby is 14 weeks old. The comparator group receives a standard leaflet, with details on the importance of glucose testing and regular follow up in pregnancy. Intervention arm-1 will receive the standard leaflet plus individualized messages, through an Interactive Voice Response (IVR) system; a type of computer-linked telephone intervention system to remind the participants about the lab test and follow-up dates. Intervention arm- 2 will have the opportunity to attend Mother and Baby Affairs (MBA) workshops, which will provide information on Gestational Diabetes Mellitus (GDM) screening and management to pregnant women and personalized counselling services. The outcome of interest is the difference in the proportion of participants completing follow-up at different points in time, among three arms.

**Discussion:**

Between the two interventions (IVR and MBA), the study results would uncover the contextually specific, timely intervention, which can increase the proportion of pregnant women followed up in public hospitals. If effective, this study will provide information on an effective intervention, useful in ensuring the success of longitudinal follow-up in the public hospitals.

**Trial registration:**

NCT03088501, Date Registered: 16/03/2017.

## Background

Longitudinal cohort studies are essential in understanding the etiological mechanisms of underlying hypotheses. It is particularly challenging to develop and sustain birth cohorts, as the observation period spans several years making it vulnerable to lose tracking subjects for several reasons. These include a change in the location of residence, lack of interest in the study, death etc. [1, 2]. Few groups are at higher risk of selective attrition, particularly ethnic minorities, those with low family income or low education, and those living in urban areas [3].

The results from prospective cohort studies can be unbiased, only if they can maintain greater compliance of follow-up. The loss to follow-up can result in biased estimates [4], if the reason for the loss is related to the outcome of the investigation. The cohort studies done in India have variable rates of loss to follow-up ranging from 14 to 82% [1, 2, 5, 6]. Continuous follow-up and ensuring retention of participants is challenging due to many reasons. These include lack of trust in the research, concerns about research design, the consent process, discordance between lay beliefs, medical practice and cost of travel, etc. This challenge is intricate given that pregnant women accessing public health facilities do not turn up for regular antenatal health checkups [7]; which are influenced by limited decision making power regarding their health, poor access, transport for routine care, perceived the poor quality of health care facilities and limited staff/financial constraints [8]. According to the National Family Health Survey (NFHS) (2014–15), only 55.5% of women in urban Bengaluru had the required four antenatal care visits during pregnancy [9].

Some reviews have reported different strategies like using a mobile phone, Interactive voice response, antenatal sessions and community-centered approaches for improving study participation and retaining a greater proportion of participants [10–17]. For example, an automated voice call was used to improve adherence to iron supplementation during pregnancy [10]. However, little is known about the effectiveness of specific retention strategies deployed in retention of mothers and infants in a birth cohort.

MAASTHI is a prospective birth cohort with the aim of assessing the effects of glucose levels in pregnancy on the risk of adverse infant outcomes, especially in predicting the possible risk markers of later chronic diseases [18]. The recruitment of the pregnant women in MAASTHI began in April 2016. The current strategy deployed in MAASTHI cohort is to follow up pregnant women for Oral Glucose Tolerance Test (OGTT), at birth and in-person child assessments at 14 weeks, annually during the year 1, 2 and 3 of the child. Currently, we are recruiting around 80 pregnant women per month, with the completion of all their records, anthropometry measurements, and OGTT. Of the eligible pregnant women, only 77% completed OGTT despite offering the test free of cost and repeated reminders by the research team to get tested for gestational diabetes. Once the OGTT is done between 24 and 36 weeks of gestation, there is no further opportunity to meet them again until the delivery. The duration without contact increases the likelihood of attrition. In the intervening period of initial contact and follow-up’s, it is essential that the participants are continuously engaged by the research staff through innovative methods in order to attain better turn up rate for follow up. Despite stringent adherence of including only the residents of the source population, nearly 20% of the women did not attend the follow-up visits at birth. In order to prevent further loss to follow-ups in subsequent visits, we are interested in exploring whether interventions involving Interactive voice response system (IVRS) and conducting mother and baby workshops can improve follow-up rates.

## Methods

The primary objective of the RCT is to evaluate the effectiveness of two interventions; IVRS and mothers and baby affairs (MBA) workshops in improving the response rate of participants for OGTT. The secondary objective is to evaluate the effectiveness of interventions in improving the follow-up rates of participants in the cohort and to also identify process indicators which contribute to observed changes in follow-up compliance and to estimate the cost-benefit analysis of the interventions offered in the study.

### Study setting

The study is conducted in a secondary level public hospitals in urban Bengaluru.

### Study population

The study population comprises of pregnant mothers in the ongoing MAASTHI cohort. By recruiting the pregnant women attending Antenatal Checkup (ANC) in a public hospital, participants will be randomly assigned to the MBA or IVRS arm or continued in the control group.

#### Inclusion criteria

Pregnant women aged 18–45 yearsPregnant mothers of 14 to 36 weeks of gestational ageAgree by providing informed consent to take part in the IVRS/MBA workshop intervention.She must be able to speak Kannada, Hindi or English.The participant must own or have sufficient access to a cell phone and should be able to operate a cell phone with a partner/ relative, who stay with her.

#### Exclusion criteria

Pregnant mothers with a history of Diabetes or Hepatitis B infection;Human Immunodeficiency Virus (HIV) positivity;Pregnant women of other gestational ages

##### Study design

The prospective study subjects of MAASTHI cohort will undergo a Randomized Controlled Trial (RCT). With the aid of a random number generator, the participants will be randomized into each arm on a 1:1:1, using a computer-generated randomization list. A parallel group design superiority trial; the sequence generation and allocation concealment will not be involved in the implementation (Fig. 1).

**Fig. 1 Fig1:**
[figure not shown]
Flowchart depicting the study design and allocation of participants to different study arms

### Blinding

After meeting the inclusion criteria, voluntarily providing informed consent, the research assistants will assign the participants to one of three study arms. Once the participant is assigned to the arm, the research staff will be recording her unique respondent identification number and the assigned arm. Research staff and pregnant women cannot be blinded because the intervention requires their participation; however, the data analyst would remain blind to the study arm assignment.

### The intervention

#### Theoretical background

The proposed RCT is evidence as well as theory based and follows a planned stepwise behavioural research approach to intervention development [19]. The self-regulation theory suggests that change in behaviour is a dynamic process, in which specific, achievable goals are set, and discrepancies between desired goals is fed back to an individual, and finally, (social) reinforcement as an essential element promotes behavioural sustainability and ongoing goal pursuit [20, 21]. The approach focuses on individual-level factors, increasing personal and normative feedback. Among others, it addresses these elements using increasing planning, performance feedback, and increasing knowledge. Self-regulation theory focuses primarily on a behavioural prediction; self-regulation models attempt to explicate the dynamic psychological mechanisms that lead to success and failure in behaving relative to some standard. Intervention package includes changes to the physical and social environment, performance feedback & goal setting, training and action planning.

The interventions are:IVRS intervention- interactive voice response.MBA intervention-Mother and baby affairsControl arm

The two proposed arms in the intervention, namely IVRS and Mother and baby affairs (MBA) workshops are designed to set goals with options for feedback to an individual; while the use of technology for (social) reinforcement is done in one arm, the other arm has peer pressure and discussion on shared goals. The interventions are expected to promote and sustain behavioural changes.

##### Interactive voice response (IVR):

IVRS are a type of computer-linked telephone intervention system that could be used to remind the participants about their medicine, treatment or follow up visit. IVR can provide individualized messages to participants and obtain feedback from participants’ responses through voice recognition or touch-tone keypad. IVR systems have shown potential for use as a tool in health care. For example, IVRS as a reminder system helped to increase preventive screening and vaccinations [22], as a means for screening high-risk pregnant women for depression [23]. IVR allows the pregnant women, their family members to interact with a computer system using a telephone. IVR systems are ubiquitous and are used for banking, flight schedules, and product ordering. Socioeconomically disadvantaged populations react favourably to and use IVR systems for extended durations [24]. Studies show that those with a lower income similar to that of our population are more likely to use IVR [25]. Through IVR, women receive a 2–3 min call that informs them about OGTT test dates, to collect their lab test reports, to know where they plan to deliver and reminds them of their follow-up visits. The IVRS will also provide health information on Gestational Diabetes Mellitus (GDM), breastfeeding and immunization. Research suggests that some socially disadvantaged populations are more likely than their advantaged counterparts to text daily [26]. Telephone technologies have an extensive reach, as mobile phone penetration is very high in the target population. In our study population, 58.6% of the women own cell phone, and everyone has at least one cell phone in their family. If the respondent does not wish to continue in the IVRS arm, they will have option to move out of this arm and continue in the control arm.

The control arm will not get the interventions but would receive a standard leaflet, with details on the importance of glucose testing and regular follow up in pregnancy; research staff would inform them the next visit date. They will be asked to meet the research team whenever they visit the hospital for their routine checkups. At each visit, the research staff will assess their general well-being and other health parameters. They will also provide standard information on health and the importance of continuing antenatal examination. If any of the interventions in the other two arms are proven successful, the control participants will receive those interventions for the subsequent follow-ups.

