### Implementation

The research staff will inform the study participants of MAASTHI birth cohort regarding the interventional trial. Upon voluntary informed consent, the research staff will screen the participants for eligibility and will randomly allocate to one of the study arms. Necessary demographic details, socioeconomic status, diet, physical activity are recorded. Participants will be randomly allocated to the study arms-, IVRS arm, MBA arm or control arm. They are invited to undergo the OGTT between 24 to 36 weeks of gestation. A portion of the blood sample will be stored at − 80 degrees for future biochemical and genetic tests.

In addition to the standard care, the MBA arm will receive intervention in the form of awareness workshop from specialist doctors. There will be role plays and quizzes, participants who win will receive small gifts from the study team.

Along with standard care, the IVRS intervention involves calls to pregnant women at specified periodic time intervals providing them with antenatal care tips, and reminder calls for OGTT and follow-up visits to the hospital. They are also given the opportunity to identify any issues or concerns that they may have with IVRS. Through IVRS, participants will be informed that the IVRS supplements, but do not replace, existing clinical services and that all emergencies should be handled by usual means. If the respondent does not wish to continue in the IVRS arm, they will have the option to move out of this arm and continue in the control arm.

The participants in the control group receive standard care; they will be explained the importance of glucose testing in pregnancy and regular follow-ups as scheduled in the study (Table 1). Baseline sociodemographic information will be collected from participants who discontinue.

**Table 1 Tab1:** Interventions for the pregnant mothers and its target behavioral correlates

Content of intervention	Operationalized as	Target Behavioral correlate
Mother and Baby Workshop(MBA)	Workshops on healthy diet, GDM, immunization, seminars, token of appreciation and a meal for the parents	Participants turning up for OGTT,follow up at delivery and 3.5 months
Interactive voice response system (IVRS)	IVRS calls to participants for reminding OGTT, follow up visit, child immunization. Regular IVRS call providing health advice to pregnant women and mothers on diet and child care	Participants turning up for OGTT, follow up at delivery and 3.5 months

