### Sample size

The current rate of screening is 77% for OGTT, and the expected rate is an increase of 10% through the interventions. In order to achieve 80% power to detect a small improvement of 10% in the screening with a significance level of 5% and 95% confidence interval, the required sample size is 50 in each arm after adding a non-response rate of 30%.

For the secondary objective, we have assumed that 50% will be followed-up at delivery. In order to achieve 80% power to detect a small improvement of 20% in follow up at delivery, with a two-sided significance level 95%, the sample size required in each arm is 104 persons [27, 28]. Assuming refusal and loss to follow up at 50%, the total number of women required per arm is 156 at delivery. Assuming higher loss to follow-up at 70% for following up children at 3 months of age, the required sample size in each arm is 265. Hence, we aim to recruit 265 pregnant women in each arm making a total of 795.

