### Statistical analysis

Descriptive statistics of participants’ baseline characteristics will be presented to assess their comparability. These statistics will be reported as a mean (SD) or median (first quartile, third quartile) for continuous variables, and count (per cent) for categorical variables. Baseline characteristics will include age, education, occupation, income, parity, gestational age, and mobile phone access. We calculate the response rate for OGTT in each of the study arms. For the primary analysis, we will compare the proportion of participants retained during the eligible period in the MBA and IVRS group with those in the control group using a Chi-square test.

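### Women who leave IVRS continue in the control arm, and the analysis does not say they are counted where they were randomised, so the comparisons with control can be biased by an unknown amount in either direction

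*Protocol article*

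**What the plan says.** Allocation is to three parallel arms; under Study design, "the participants will be randomized into each arm on a 1:1:1" basis. The description of the IVR intervention then provides that if a woman does not wish to continue with IVRS, "they will have option to move out of this arm and continue in the control arm". The Implementation section says the same: "they will have the option to move out of this arm and continue in the control arm". No matching option is described for MBA or for control.

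Under Statistical analysis, the primary analysis is a chi-square test that will "compare the proportion of participants retained during the eligible period in the MBA and IVRS group with those in the control group". No sentence says whether these groups are formed by assignment or by the arm a woman ends in. The Outcome measures section takes as denominator the women due for OGTT, and for the secondary outcomes the eligible live births and the eligible infants at 3.5 months. None of these is tied to the arm assigned. The Blinding section says that the assigned arm is recorded for each woman.

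**The concern.** The protocol does not merely allow a woman to stop the calls. It says which arm she is in afterwards, and the analysis then uses that arm as the comparator. If the text is followed literally, a self-selected group moves one way, out of IVRS and into control, after randomisation.

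The primary outcome is attendance for OGTT, and the calls being declined are partly reminders to attend. Willingness to keep receiving them may therefore be related to the outcome. If switchers attend less often than average, the IVRS rate rises and the control rate falls together. If they attend more often, the reverse happens. The MBA comparison is affected as well, because it uses the same control rate. The test would no longer hold its 5% error rate, and blinding the analyst does not correct denominators.

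**Working it through.** **Inputs from the protocol article.** The Sample size section gives the baseline rate and the target: "The current rate of screening is 77% for OGTT, and the expected rate is an increase of 10% through the interventions". I read the increase as absolute, 77% to 87%. The same section gives the arm size: "we aim to recruit 265 pregnant women in each arm making a total of 795".

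**The plan's own figures.** The document gives no figure for switching, so there is none to reproduce. The 265 can be traced: two proportions, 50% against 70%, two-sided 5%, 80% power, continuity-corrected, give 103 (104 stated); 104 × 1.5 = 156; 156 × 1.7 = 265.2. For the primary outcome the section states 50 per arm. I cannot reproduce that figure (77% against 87% needs 231 per arm before inflation). It is a separate matter and is not used here.

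**Assumptions, not in the document.** s = share of the IVRS arm that switches (5%, 10%, 20%). q = share of switchers who complete OGTT (50%, 60%, 70%, with 77% and 100% as reference cases).

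**Formulas, no true effect, switchers counted as controls.**

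- IVRS rate = (0.77 − s·q) / (1 − s)
- Control rate = (0.77 + s·q) / (1 + s)
- Spurious IVRS-minus-control difference = 2s(0.77 − q) / (1 − s²)

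Worked case, s = 10%, q = 50%: IVRS = (0.77 − 0.05)/0.90 = 80.0%; control = (0.77 + 0.05)/1.10 = 74.5%; difference = 0.2 × 0.27/0.99 = 5.5 points. At s = 20%, q = 50%: 0.67/0.80 = 83.8% and 0.87/1.20 = 72.5%; difference 11.2 points.

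| Switchers' OGTT rate q | s = 5% | s = 10% | s = 20% |
|---|---|---|---|
| 50% | +2.7 | +5.5 | +11.2 |
| 60% | +1.7 | +3.4 | +7.1 |
| 70% | +0.7 | +1.4 | +2.9 |
| 77% | 0 | 0 | 0 |
| 100% (all leave after OGTT) | −2.3 | −4.6 | −9.6 |

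**False-positive rate** of the two-sided 5% test, 265 randomised per arm: at q = 50%, about 12%, 32% and 85% for s = 5%, 10% and 20%; at q = 70%, about 5%, 7% and 12%.

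**When the 10-point target is reached.** Setting the difference to 0.10 gives q = 0.77 − 0.10(1 − s²)/(2s). This is 27.5% at s = 10%, 44% at s = 15% and 53% at s = 20%. At s = 5% it is negative, so the target cannot be reached.

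**Effect on MBA against control.** The control rate falls by s(0.77 − q)/(1 + s). At q = 50% this is 0.1 × 0.27/1.1 = 2.5 points for s = 10% and 0.2 × 0.27/1.2 = 4.5 points for s = 20%, which would appear as an MBA benefit.

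**Analysed as randomised.** With no true effect the expected difference is 0 and the error rate is 5%, whatever s and q are. If those who stop calls gain nothing from IVRS, a true 10-point effect becomes 10 × (1 − s).

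**The case against.** The strongest reply is that the document never says switchers are counted as controls. Both sentences sit in the intervention and implementation text and may describe only the care a woman then receives. The assigned arm is recorded, and naming the analysis set is commonly left to a SAP, which is not shown. This stands in part: a reader might infer that an as-treated analysis is planned, and the text does not establish that. But the point does not rest on silence alone. The protocol places these women in the control arm and then compares with the control group, so a SAP that analysed by assignment would have to override that natural reading.

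A reader might also infer that the rule must inflate the IVRS effect. The document does not support this. IVRS calls continue after OGTT with follow-up reminders and child-care advice, and a woman who leaves then has already completed the primary outcome. Counting her as a control works against IVRS.

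Nor does the document support a claim that the bias will match the target effect. In the table, only 20% switching with 50% completion passes 10 points. Nothing fixes the switching share: the Discussion concedes that most intended users ignore IVR systems, but ignoring calls is not asking to be moved, and the inclusion criteria require consent and phone access.

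Finally, no head-to-head test of IVRS against MBA is specified, so the point concerns the two comparisons with control.

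**Conclusion.** The concern holds in this form: the protocol moves IVRS leavers into the control arm and does not say they are analysed in the arm they were randomised to. Followed literally, that undoes the randomised comparison for IVRS and contaminates the control rate for MBA. The direction is not determined by the document. The size ranges from nothing, if switchers complete at the average rate, through 1 to 7 points at 10% to 20% switching with 60% to 70% completion, to about 11 points at 20% switching with 50% completion. These figures rest on assumed values of s and q, on a 77% rate in both arms, and on 265 evaluable women per arm. Because the size cannot be bounded in advance and the assigned arm is already recorded, the wording should be corrected rather than left to interpretation.

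**What to change.** 1. In the IVR intervention text and in Implementation, replace the switching sentence: a woman may stop IVRS calls at any time, but she remains in the IVRS arm for follow-up and analysis.
2. In Statistical analysis, state that every comparison is by randomised arm, with the existing outcome denominators (women due for OGTT, eligible live births, eligible infants at 3.5 months) applied within each randomised arm. This leaves the outcome definitions as they are. Requiring all randomised women in every denominator would change them and is a different question.
3. Report the number who stop calls as a process indicator, which fits the stated secondary objective.

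No new data are needed, and a woman's freedom to stop calls is unchanged. The cost is dilution. If those who stop gain nothing from IVRS, a true 10-point effect becomes 9 points at 10% stopping, with power at 265 per arm of about 76% against 85% with none stopping. At 20% stopping it becomes 8 points, with power about 65%. That loss is not trivial if stopping is common, but the test keeps its 5% error rate.
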